#### Data Monitoring

The establishment of a Data Monitoring Committee is not necessary given the study characteristics. No interim analyses will be conducted.

#### Harms

Exercise-related adverse effects (e.g., chest pain, dizziness, skeletal muscle injuries) will be recorded during the training sessions. No other unintended effects related to nutritional supplementation or psychological intervention are expected.

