Frailty is very frequent among CKD patients included in the waitlist for deceased donor KT, and post-transplant outcomes are worsened in those frail recipients. Moreover, frailty and poor fitness powerfully predict mortality, kidney graft survival, and healthcare utilization after KT. Thus, we hypothesize that a pre-transplant clinical framework for multimodal prehabilitation interventions including physical therapy, nutritional measures, and psychological support could improve patient retention and compliance, better mitigate the effects of frailty and poor fitness after KT, and improve main outcomes in frail CKD patients.

The main objective of this study is to assess effectiveness, feasibility, and safety of multimodal prehabilitation (exercise, nutritional plans, and psychological advice) in KT candidates in the context of a randomized controlled clinical trial. There are three specific objectives: (1) to study the potential effects of multimodal prehabilitation as a prognostic variable to predict the 90-day primary endpoint based on clinical and functional outcomes achieved in frail and non-frail KT candidates; (2) to assess the feasibility and safety of a multimodal prehabilitation program, with especial emphasis on the exercise component in KT candidates; and (3) to assess differences in exercise capacity, muscle function, functional status, and health-related quality of life in frail and non-frail candidates at 1-year post-KT follow-up.

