## Methods and Analysis

### Trial Design

The FRAILMar Study is a controlled randomized clinical trial in candidates to KT assigned to the intervention group (multimodal prehabilitation) or control group (standard medical care), with an allocation ratio of 1:1, in a superiority framework. Results are stratified by frail and non-frail patient status. The study protocol is described following the Standard Protocol Items: Recommendations for Interventional Trials (SPIRIT) Statement (3).

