#### Physical Exercise

The exercise component will consist of 1-hour sessions, three times per week for 8 weeks (total 24 sessions). Two of the weekly sessions will be supervised by a physical therapist and the third will be performed unsupervised at the patient's home. Patients will choose between on-site or home-based exercise with the physical therapist; in the case of exercising at home, patients will receive a training kit (cycle ergometer, weights, elastic bands, respiratory muscle trainer); the therapist will telematically supervise the sessions using an internet video call platform. Time schedules for conduction the intervention are detailed in Table 1.

**Table 1 T1:** Time schedules for conducting the intervention.

	**Mon**	**Tues**	**Wed**	**Thurs**	**Fri**	**Sat**
Mornings	Supervised		Supervised		Unsupervised	
Afternoons	Supervised		Supervised		Unsupervised	
Mornings		Supervised		Supervised		Unsupervised
Afternoons		Supervised		Supervised		Unsupervised

All patients will be given access to audiovisual material to support the unsupervised sessions. Each training session will consist of four elements: (1) warm-up (5 min); (2) continuous aerobic training performed on a cycle ergometer (20 min at 60% workload peak, increasing by 5 watts weekly if tolerated); (3) muscle strength exercises of upper and lower limbs (three sets of 10 repetitions of biceps curls, back and shoulder presses, hip flexion and knee extension, and self-weight squats; initial workload will be of 0.5 Kg and increase by 0.5 Kg weekly if tolerated); (4) inspiratory muscle training [five sets of 10 repetitions followed by 1–2 min of unloaded recovery breathing, once a day, 7 days a week for 8 weeks, using an inspiratory muscle trainer (Orygen Inspiratory One-way Valve, Forumed, Spain) at a rate of 15–20 breaths/min; training loads will be set at 30% of maximal inspiratory pressures (PImax) and adjusted weekly by 10 cmH_2_O if tolerated]; and (5) muscle stretching cool-down (5 min).

After completing the 8-week sessions, patients will be encouraged to continue exercising at home or community sports facilities, and will receive coaching from the physical therapist once a month till KT. All study participants shall be removed from the KT waitlist during this period, and re-included after the 12-week assessment, respecting their original placement on the waitlist.

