The proportion of non-frail patients at the end of the intervention and during pre-KT follow-up.Exercise capacity estimated by peak oxygen uptake (VO2peak) and workload (Wpeak), achieved in a cardiopulmonary effort test (CPET) expressed in mL/Kg/min and watts, respectively. A VO2peak increase of 1.5 mL/Kg/min (minimum clinically important difference) is expected to be achieved after intervention (30).Gait speed in a four-meter test.Distance traveled in a 6-min walking test (6MWT).Physical activity in the past seven days, estimated with accelerometry (total energy expenditure in Kcal, activity-related energy expenditure in MET, number of steps); total activity time will be classified as sedentary, light, moderate, and vigorous according to the Freedson Adult algorithm (31).Physical activity in the past month, assessed with a validated questionnaire.Peripheral muscle strength estimated with maximal isometric contraction of the dominant hand flexor muscles (in upper limbs) and quadriceps muscles (in lower limbs).Respiratory muscle strength estimated with inspiratory and expiratory muscle pressures (PImax and PEmax, respectively).Lean mass assessed by dual-energy X-ray absorptiometry (DXA) and bioelectrical impedance analysis (BIA).Muscle quantity and muscle quality assessed with the ultrasound parameters recommended by the Sarcopenia through Ultrasound (SARCUS) group in its 2020 update (32).Performance in activities of daily living.Performance in instrumental activities of daily living.Mindfulness dispositional traits.Patient satisfaction with multimodal prehabilitation.

Secondary **long-term outcomes** will include improvement in:

Proportion of well-nourished patients.Depression and anxiety symptoms.Personality traits.Health-related quality of life.

**Feasibility variables** will also be analyzed:

Losses to follow-up (patients not completing the follow-up assessments).Exercise tolerance (patients who adapt to intensity modification).Safety, estimated by the absence of any adverse events during the training sessions.Physical training participation (yes/no) and attendance (>80% attended sessions or home-based exercise).Mindfulness participation (yes/no) and attendance (>80% attended sessions or home-based exercise).Adherence to each of the multimodal prehabilitation components (physical activity habits, diet recommendations, and mindfulness habits).

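### Safety of the whole programme is an objective, but the stated safety variable covers only training sessions, so the arms cannot be compared on safety before transplantation

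*Protocol article*

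**What the plan says.** The Introduction of the protocol article gives the main objective as "to assess effectiveness, feasibility, and safety of multimodal prehabilitation". The second specific objective is "to assess the feasibility and safety of a multimodal prehabilitation program", with particular emphasis on exercise. The object of the safety claim is therefore the three-component programme, not the exercise session alone.

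Safety is given an operational definition in two places, and they agree:

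- Study Outcomes, feasibility variables: "Safety, estimated by the absence of any adverse events during the training sessions".
- Harms: exercise-related effects "will be recorded during the training sessions". On the other two components it says: "No other unintended effects related to nutritional supplementation or psychological intervention are expected".

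The comparator, in Trial Design, is a "control group (standard medical care), with an allocation ratio of 1:1". Standard Medical Care describes usual treatment plus activity advice, with no training sessions.

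The section on discontinuing or modifying interventions mentions serious adverse events resulting from the intervention. It states what follows from one (the patient stops the intervention and stays in the intention-to-treat analysis), but not how such events are ascertained in either arm.

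**The concern.** The safety variable depends on an exposure that only one arm has. Waitlisted candidates, many on haemodialysis and some frail, can be expected to have falls, cardiac symptoms, hospital admissions and deaths whatever arm they are in. Without a concurrent rate from controls, events in the intervention arm cannot be attributed to the programme or cleared of it.

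The window is also narrower than the intervention. Part of the programme takes place away from sessions, and two of its three components are not sessions in this sense at all. A report of no adverse events during training would describe tolerability of the exercise sessions. It would not answer the second specific objective, which concerns the programme. A later analysis plan cannot repair this, because it cannot recover events that were not collected.

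**Working it through.** The plan gives no figure for this point, so there is none to reproduce. The check counts what the stated window covers.

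**1. Who can contribute.** Sample Size plans 23 frail and 46 non-frail patients per arm: 23 + 46 = 69 per arm, 138 in total. The share with no training sessions is 69/138 = 50%. For these patients the variable is undefined, not zero.

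**2. Sessions (Physical Exercise).** Three a week for 8 weeks: 3 × 8 = 24.
- Supervised: 2 × 8 = 16.
- Unsupervised at home: 1 × 8 = 8, or 8/24 = 33%.

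The 8 unsupervised sessions belong to the 24, so they fall inside the stated window. Their weakness is that nobody observes them and no route for reporting an event is given.

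**3. Inspiratory training (Physical Exercise).** Daily for 8 weeks: 7 × 8 = 56 days. Table 1 puts each session on a separate day, so:
- Days with no session: 56 − 24 = 32, and 32/56 = 57%. These are outside the window.
- Days with no supervised session: 56 − 16 = 40, and 40/56 = 71%.

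**4. Programme components against the window.**

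| Element | Where stated | In the window? |
|---|---|---|
| 16 supervised sessions | Physical Exercise | Yes, observed |
| 8 unsupervised sessions | Physical Exercise | Nominally; no observer or stated reporting route |
| Inspiratory training, 32 non-session days | Physical Exercise | No |
| Encouraged exercise after week 8 until transplantation | Physical Exercise | No |
| Supplements, including maintenance after week 8 | Nutritional Supplementation | No |
| Psychology visit and later mindfulness group | Psychological Advice | No |

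**5. Calendar time.** The primary composite (Study Outcomes) is assessed at day 90 after transplantation. It includes all-cause death, non-elective readmission and surgical complications, and applies to both arms. Before transplantation there is no equivalent. Sample Size treats mortality after listing and medical exclusion from the list as part of the 20% allowance for losses. They are not listed as safety outcomes.

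The uncovered period is therefore from randomisation to transplantation, and it contains the whole intervention.

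**The case against.** The strongest reply is that this is a two-sentence Harms section in a journal article. It does not say that nothing else is recorded, and adverse-event forms and serious-event reporting are usually left to the full protocol. The provision for serious adverse events presupposes some way of learning about them. Intervention patients meet a therapist twice a week and then monthly, so much would come to light informally. Safety is listed among the feasibility variables, the objective stresses exercise, and in-session tolerability fits that emphasis.

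Part of this stands. Other events may well be recorded somewhere. But the article does not leave the safety variable open: it defines it, twice, in the same terms. Informal disclosure to therapists occurs only in the intervention arm, so it gives no comparison.

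Several stronger readings are tempting and are not supported:

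- **That a third of the sessions are excluded from recording.** They are counted among the 24. That events there go unseen is an inference.
- **That 57% of safety information is lost.** The figure counts days of one component. It measures neither missed events nor exposure to the whole programme.
- **That nothing is captured in controls.** This is true of the in-session variable only; the composite covers both arms after transplantation.
- **That waitlist removal is an uncounted harm of prehabilitation.** The text reads "All study participants shall be removed from the KT waitlist during this period". It applies to both arms, so it is a consequence of taking part in the trial, and a between-arm comparison would not isolate it.
- **That the result is favourable by construction.** Absence of any event is a strict criterion, which a single episode of dizziness would fail.

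**Conclusion.** The concern holds in limited form. The stated safety variable does not match the stated safety objective. Followed as written, it allows no between-arm safety comparison before transplantation, because half of the planned participants cannot have an event under the definition. In the intervention arm it omits inspiratory training on 32 of 56 days, later home exercise, supplements and the psychological component. The post-transplant period is not affected for death, non-elective readmission and surgical complications.

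This rests on two assumptions: that the full protocol uses the same safety variable as the article, and that sessions fall on separate days as in Table 1. The point should be corrected, but it does not touch the primary endpoint.

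Expectations of the corrected data should be modest. With 69 per arm the comparison would be descriptive. Even no events of a given kind among 69 patients leaves a one-sided 95% upper limit of 1 − 0.05^(1/69) = 4.2%.

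**What to change.** Change the safety variable in Study Outcomes and in Harms, in the same words, to:

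- serious adverse events, including death, hospitalisation and delisting for medical reasons (kept distinct from the trial's own temporary removal from the list); and
- exercise-relevant adverse events, such as falls, injuries and cardiac symptoms.

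Collect these in both arms from randomisation to transplantation, with one standard question at contacts that already exist: the assessments after the exercise period and every 6 months (Study Outcomes), and the telephone calls before each assessment (Data Collection Methods). This assumes that controls attend and are called on the same schedule. Report events by arm per patient-month.

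The intervention arm has many more contacts and the trial is open. The between-arm table should therefore use only events elicited at the common contacts. In-session events should be kept as an additional intervention-arm tolerability table, with a stated way for patients to report events from unsupervised sessions.

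If this is not done, the objective and conclusion should be limited to in-session exercise tolerability.

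The cost is modest extra data entry, plus background events unrelated to the programme. Stopping at transplantation avoids duplicating what the composite already records.

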#### Auditing

The principal investigators will be in charge of auditing the trial procedures (assessments and interventions) within the 1st month of the project and every 6 months thereafter until completing data collection.

## Discussion

Frailty in CKD patients displays a unique constellation of features that characterize this special population, including muscle wasting, anorexia, protein energy wasting, inflammation, oxidative stress, catabolic/anabolic hormone imbalance, metabolic acidosis, and other cellular alterations. Intervention is essential to improve quality of life for frail CKD patients, regardless of their age. Studies of post-transplant physical therapy intervention have been met with limited success, in large part due to high dropout rates. A pre-transplant clinical framework that provides multimodal prehabilitation interventions including physical therapy, nutritional measures, and psychological support may improve patient retention and compliance, better mitigate the effects of frailty and poor fitness after KT, and improve main outcomes in frail CKD patients.

Prehabilitation is more challenging in KT than in other surgical settings because the transplantation date is usually unknown. Furthermore, not all KT candidates can combine prehabilitation sessions with their HD schedules. Work schedules and geographic distance can also limit participation. In a recent survey, only 25% of HD patients were able to exercise without difficulty; the major barriers for the remaining patients were feeling too tired (55%), shortness of breath (50%), and too weak (49%) (65). If patients were to exercise, they preferred to exercise at home (73%) using a combination of aerobic and resistance training (41%), regardless of modality or age category. Finally, an extremely large sample size would be required to assess long-term outcomes like death or graft loss, as well as other important clinical outcomes that result from increased physical activity (66–68).

The main limitation is the low physical profile of many frail CKD patients, even those scheduled for KT. Consequently, some patients will not consent to undertake the intervention program and the adherence could be low, with high dropout rates. Efforts will be made by the research team to facilitate all logistical requirements and explain the strong potential benefits to the patients and their families. The process of designing the prehabilitation plan will take account of the final users' perspective in order to achieve a realistic, acceptable, user-friendly approach that covers patient needs and preferences and avoids simplistic solutions that ignore the patients' reality.

## Ethics Statement

The FRAILMar Study protocol and the informed consent have been approved by the local Ethics Committee of the Hospital del Mar Research Institute, Barcelona, Catalonia, Spain (Nr. 019/8623/I). National and international research ethics guidelines, including the Declaration of Helsinki, and current confidentiality law concerning personal data (Spanish Organic Law 3/2018, and European Parliament and Council Regulation EU 2016/619) will be followed. Detailed and understandable oral and written information will be provided, and informed consent to participate will be signed by all participants. Important protocol modifications will be communicated to involved parties (researchers, participants, and trial registry. The principal investigators will have access to the final trial dataset. The trial results will be communicated to participants, healthcare professionals, and patient groups (e.g., scientific meetings, publications in peer-reviewed journals). Informed consent is available in Catalan and Spanish languages upon request.

## Abbreviations

ATS: American Thoracic Society
BIA: Bioelectrical impedance analysis
CES-D: Center for Epidemiologic Studies Depression
CKD: Chronic kidney disease
CPET: Cardiopulmonary effort test
DXA: Dual-energy X-ray Absorptiometry
ESRD: End-stage renal disease
EWGSOP: European Working Group on Sarcopenia in Older People
FFMQ: Five Facets Mindfulness Questionnaire
GAD-7: Generalized Anxiety Disorder seven-item questionnaire
GLIM: Global Leadership Initiative on Malnutrition
HADS: Hospital Anxiety and Depression Scale
HD: Hemodialysis
KT: Kidney transplantation
MBCT: Mindfulness Based Cognitive Therapy
MLTPAQ: Minnesota Leisure Time Physical Activity Questionnaire
MUST: Malnutrition Universal Screening Tool
PImax: Maximal inspiratory pressure
PEmax: Maximal expiratory pressure
SARC-F: Strength, Assistance in walking, Rise from chair, Climb stairs, and Falls
SARCUS: Sarcopenia through Ultrasound
SF-36: Short Form 36-item health questionnaire
SNAQ: Subjective Nutritional Assessment Questionnaire
SPIRIT: Standard Protocol Items, Recommendations for Interventional Trials
TCI: Temperament and Character Inventory
VO_2peak_: Peak oxygen uptake
W_peak_: Peak workload
6MWT: 6-min walking test.
